## 6.7 Study Procedures

---

### 6.7.1 Screening and Enrollment

---

Screening and enrollment is schematically shown in Figure 1.

Subjects with acute SCI who present to a participating center within 12 hours of injury will be screened for inclusion. Prior to any screening procedures, subjects will sign the ICD. If the subject meets all of the eligibility criteria, he/she will be randomized and enrolled into the study. The randomization will occur as soon as possible after the eligibility has been determined and the first dose of Investigational Drug will be administered not later than 12 hours from the time of injury. Given the nature of this study and very short period available for the screening, in some rare instances a patient may be enrolled and receive the Investigational Drug prior to receipt of all screening laboratory results. In such rare cases, a clinically significant abnormal value for any of the tests may result in the discontinuation of the patient.

The subject will be considered enrolled into the study when the randomization occurs, and the first dose of study medication is administered.

**Figure 1 Screening and enrollment design**

[figure not shown]

## 6.7.2 Investigational Drug Dose and Administration

### 6.7.2.1 Dose

Subjects will receive a total of 28 doses of Investigational Drug, administered twice a day, for a total of 14 days. The riluzole group will receive riluzole in a dose of 100 mg at 0 hours and 12 hours (doses 1 and 2) followed by 50 mg doses every 12 hours for the next 13 days (doses 3 - 28). The control group will receive placebo capsules in a dose of two capsules at 0 hours and 12 hours (doses 1 and 2) followed by one capsule every 12 hours for the next 13 days (doses 3 to 28).

### *6.7.2.2 Administration of Study Drug*

---

The first two doses of study drug must each be given according to the Protocol schedule (i.e. at 0 hours and 12 hours). The third dose can be administered to align with the standard hospital medication administration schedule. If the next standard hospital medication administration time falls 4 or more hours after the second dose, the third dose should be administered at that time. If the next standard hospital medication administration time falls less than 4 hours after the second dose, that time shall be skipped and the third dose should be administered at the second standard hospital medication administration time. Doses 4 through 28 should be administered every 12 hours.

For example, a hospital's standard medication administration times are 09:00 (9:00 AM) and 21:00 (9:00 PM).

- Patient A's first dose is given at 03:30 (3:30 AM) and the second dose is given at 15:30 (3:30 PM). More than 4 hours elapse before the next standard medication administration time, so the third dose is given at 21:00 (9:00 PM), the fourth dose at 09:00 (9:00 AM) and afterwards every 12 hours.
- Alternatively, Patient B's first dose is given at 06:00 (6:00 AM) and the second dose is given at 18:00 (6:00 PM). The standard medication administration time (21:00) is only 3 hours after the second dose, so the third dose is given at 09:00 (9:00 AM) the next day, the fourth dose at 21:00 (9:00 PM) and afterwards every 12 hours.

For subjects who are unable to receive oral medications, the filler from each capsule will be mixed with 3 mL of water and will be delivered via nasogastric tube.

The investigational drug should be taken at least an hour before, or two hours after, a meal to avoid a food-related decrease in bioavailability. If the subject is on a continuous feeding schedule via nasogastric tube, it is recommended that feeding is stopped to accommodate the above drug administration schedule, as long this is not clinically contraindicated. If there is a clinical contraindication to stop feeding via nasogastric tube, the drug should be administered without interruption of continuous feeding.

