| Intervention | 
Drug:
 
 
1. Experimental: riluzole 100 mg BID first 24 hours followed by 50 mg BID for 13 days
 
2. Control: placebo
 
                                                                                                                                                                                                                                                                                                                                                                                                                                                                                                                                                                                                                                                                                                                                                                                                                                                                                                                                                                                                                                                                                                                                                                                                                                                                                                                                                                                                                                                                                                                                                                                                                                                                                                 |

|                                     |                                                                                                                                                                                                                                                                                                                                                                                                                                                                                                                                  |                                |

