### 5.2.2 Pharmacology and Pharmacokinetics of Riluzole

In human studies, riluzole has been administered intravenously in a single dose of 50 mg and orally in a variety of dose combinations ranging from single doses of 25 mg, 50 mg and 100 mg, incremental doses up to 300 mg and in repeated doses of 25 mg, 50 mg and 100 mg BID [20]. Riluzole is rapidly absorbed from the gastrointestinal tract and reaches maximum plasma concentration ( $C_{\max}$ ) within approximately 1 hour after oral administration [20, 21]. Studies show that when administered at a dose of 50 mg BID, the  $C_{\max}$  is achieved, on average, at 0.75 - 0.9 hours (SD = 0.5 hours) [20, 21]. After reaching the  $C_{\max}$ , the plasma concentration rapidly declines [20-22]. The steady state through plasma concentrations are achieved within five days [20]. At a dosage of 50 mg BID, the terminal elimination half-life was 14.7 hours [20]. Several studies have reported that men have lower peak and trough levels of riluzole compared to women [21, 23]. Riluzole is highly bound to plasma proteins (96%) and is metabolized in the liver by an enzyme of the cytochrome P450 (CYP) family; specifically by a member of the CYP 1A2 subfamily, whose substrates include acetaminophen, caffeine and warfarin.

A pivotal, double-blind, randomized, controlled trial of riluzole in patients with amyotrophic lateral sclerosis (ALS) has investigated efficacy and safety of riluzole in doses of 25 mg BID, 50 mg BID and 100 mg BID [24]. The dose of 25 mg BID was not significantly better than placebo. Doses of 50 mg BID and 100 mg BID were superior to placebo, with no difference between the two doses. The dose 50 mg BID had the best benefit/harm ratio.

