### 6.1 Study Scope

---

This is an international, multi-center, prospective, double-blinded, randomized, placebo-controlled Phase II/III clinical trial to evaluate if riluzole at a dose of 100 mg BID for the first 24 hours followed by 50 mg BID for 13 days is superior to placebo in subjects with acute traumatic SCI.

The study will involve up to 35 investigational sites and enroll 351 subjects (includes 10% allowance for attrition). A randomization ratio of one riluzole subject to one placebo-controlled subject (1:1) will be utilized. The sample size may change during the interim analysis due to the adaptive statistical design.

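### The dose 3 alignment allowance in section 6.7.2.2 is missing from the regimen statements, and in the protocol's own example it puts 250 mg rather than the implied 200 mg into the first 24 hours

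*Protocol*

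**What the plan says.** The regimen is stated in several places. Protocol section 6.1 sets out to evaluate "riluzole at a dose of 100 mg BID for the first 24 hours followed by 50 mg BID for 13 days". The Synopsis (section 4, under Aim and under Intervention) and section 6.2 say the same in substance. Section 6.7.2.1 adds clock times for the riluzole arm: "100 mg at 0 hours and 12 hours (doses 1 and 2) followed by 50 mg doses every 12 hours for the next 13 days". It also fixes the course: "Subjects will receive a total of 28 doses of Investigational Drug, administered twice a day, for a total of 14 days". None of these statements mentions an exception.

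Section 6.7.2.2 then treats dose 3 separately. Doses 1 and 2 must be given at 0 and 12 hours. Dose 3 *can* be aligned with the hospital's usual drug rounds. The rule applies when an upcoming "standard hospital medication administration time falls 4 or more hours after the second dose, the third dose should be administered at that time". Where that round is less than 4 hours away, it is skipped and dose 3 goes to the round after it. Doses 4 to 28 follow every 12 hours.

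Two worked examples use rounds at 09:00 and 21:00. Patient A is dosed at 03:30, 15:30 and 21:00. Patient B is dosed at 06:00, 18:00 and 09:00 the next day.

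**The concern.** Under section 6.7.2.1, dose 3 falls 12 hours after dose 2, so two 100 mg doses make up the whole of the first 24 hours. Under section 6.7.2.2, the first 50 mg dose can fall inside that period. The protocol therefore describes one first-day exposure in its objective and allows two in its dosing instructions, with the clock time of the first dose deciding which one a subject gets.

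Three things are at stake. The regimen named in the objective and scope should be the regimen delivered. The risk description should cover the first-day total that the instructions permit. And the per-protocol population (section 7.13.4) is limited to patients treated entirely in line with the protocol, which is easier to apply if the protocol gives one account of when dose 3 is due.

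**Working it through.** **Inputs.** Dose sizes, the 0 and 12 hour times, the 28 doses and the 14 days come from section 6.7.2.1. The 4-hour rule, the 09:00 and 21:00 rounds and both patients come from section 6.7.2.2.

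**1. The plan's own figures reproduce.** Doses: 2 + 13 × 2 = 28. Days: 28 / 2 = 14. Dose 3 is nominally due at 12 + 12 = 24 h after dose 1. The amount given before that is 2 × 100 = 200 mg; this total is implied and not printed. Applying the 4-hour rule gives 21:00 for Patient A and 09:00 for Patient B, as stated.

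**2. The worked examples against the stated regimen.**

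| | Section 6.7.2.1 | Patient A | Patient B |
|---|---|---|---|
| Dose 2 to dose 3 | 12 h | 21:00 − 15:30 = 5.5 h | 18:00 to 09:00 = 15 h |
| Dose 1 to dose 3 | 24 h | 21:00 − 03:30 = 17.5 h | 06:00 to 09:00 next day = 27 h |
| Total in first 24 h | 200 mg (implied) | 100 + 100 + 50 = 250 mg | 100 + 100 = 200 mg |

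Patient A's dose 4, at 09:00 the next day, is 29.5 h after dose 1, so the 24-hour total stays at 250 mg. The ratio is 250 / 200 = 1.25.

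**3. The range of intervals.** Let U be the wait in hours from dose 2 to the next round, with rounds 12 h apart, so U lies between 0 and 12.

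- If U ≥ 4, dose 3 comes U hours after dose 2 (4 to 12 h), which is 12 + U hours after dose 1 (16 to 24 h).
- If U < 4, dose 3 comes 12 + U hours after dose 2 (12 to just under 16 h), which is 24 + U hours after dose 1 (24 to just under 28 h).

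**4. The share with a third dose inside 24 h.** The documents give neither the distribution of first-dose clock times nor the share of sites that would align. Assume that U is uniform on 0 to 12, that rounds are 12 h apart and that every site aligns. Then P(U ≥ 4) = 8/12 = 67%. With rounds at 09:00 and 21:00, the share depends on when first doses fall:

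- 100% for first doses between 09:00 and 17:00 or between 21:00 and 05:00.
- 0% for first doses between 05:00 and 09:00 or between 17:00 and 21:00.
- 50% to 83% across the four six-hour bands of the day starting at midnight.

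The possible range is therefore 0 to 100%, and sites that do not align lower the share. The 24-hour cut is also sharp, because a dose at 23 h 50 min counts the same as one at 16 h. Under the same assumptions, the share with dose 3 more than 2 h early (U from 4 to 10) is 6/12 = 50%.

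**5. What does not change.** The course total is 2 × 100 + 26 × 50 = 1500 mg for both patients and for the stated regimen. Dose 28 falls at 17.5 + 25 × 12 = 317.5 h for Patient A and 27 + 25 × 12 = 327 h for Patient B, against a nominal 24 + 25 × 12 = 324 h.

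**The case against.** The strongest reply is that section 6.7.2.2 is a deliberate, specific exception. It directly follows section 6.7.2.1 under the same heading, names dose 3, sets a 4-hour floor and gives two examples. The nursing instruction in section 6.7.7.12 sends staff to section 6.7.2 for further explanation. What moves is the timing of one scheduled 50 mg dose. This largely stands. It does not explain why the sections that define the tested regimen omit an exception that changes the first-day total.

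Several stronger readings are tempting, and the documents do not support them.

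- *Two-thirds, or most, of riluzole subjects would receive 250 mg on the first day.* The 67% rests on the assumptions in the working, including full use of an alignment introduced with *can*.
- *Following either section breaches the other.* Because alignment is permitted, a site that keeps dose 3 at 24 h can be read as complying with both, although *should* governs the timing once a site chooses to align.
- *The total exceeds anything in the cited experience.* Section 5.2.2 lists "repeated doses of 25 mg, 50 mg and 100 mg BID", but the same sentence also cites incremental doses up to 300 mg. A one-off 24-hour sum is not comparable with a sustained daily dose.
- *The alignment rule is what leaves the safety background short.* The earlier spinal cord injury study used 50 mg every 12 hours (section 5.2.6), and Table 6 covers 100 mg/day. Neither matches the stated 100 mg twice daily first day, so that gap exists without the rule.
- *The treatment comparison is biased.* The rule is the same in both blinded arms, and no consequence for the day-180 analysis follows from it.
- *The consent document is deficient.* Its text is not available for review, so this cannot be judged.

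**Conclusion.** The point holds as an unreconciled inconsistency about first-day exposure. For Patient A this needs no assumption: 250 mg within 17.5 h and a 5.5 h interval, against an implied 200 mg in 24 h and a stated 12 h interval. The interval range of 4 to just under 16 h assumes rounds 12 h apart, as in the example. How many subjects would be affected is unknown. The matter deserves correction because the documents should describe the regimen being tested, but it does not threaten the validity of the between-arm comparison.

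**What to change.** Reconcile the Synopsis (Aim and Intervention), sections 6.1 and 6.2, and sections 6.7.2.1 and 6.7.2.2, so that the first-24-hour total and the interval between dose 2 and dose 3 are the same wherever they are stated or implied. Which statement governs is for the sponsor's clinical team; this review takes no view. If the alignment allowance stays, the regimen statements and the risk section (section 8) should state it, with the resulting first-24-hour total and interval range.

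The cost is protocol wording and site dosing instructions. The downside is either less flexible nursing times for one dose or a less tidy statement of the regimen.

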### *6.7.2.3 Monitoring Liver Chemistries and Investigational Drug Discontinuation*

---

Liver chemistries will be monitored in all subjects as riluzole can increase serum aminotransferase, even in patients without a prior history of liver abnormality. Enzymes (ALT, AST, ALP and GGT) and serum bilirubin will be monitored on days 3, 7 and 14. The procedure to follow-up subjects with elevated enzymes and decision to discontinue medication will be made in accordance with the FDA Guidance for Industry "Drug-Induced Liver Injury: Premarketing Clinical Evaluation," 2009.

#### **Follow-up of subject with increase of serum AT to >3xULN**

- If enzyme elevation is greater than 3 times normal, repeat testing within 48 - 72 hours including ALT, AST, ALP and bilirubin to confirm the abnormalities and to determine trend.

- Monitor for clinical symptoms of hepatic injury such as nausea, vomiting, fever, right upper quadrant pain or tenderness, rash or eosinophilia (> 5%).
- Other clinical maneuvers and tests should be per standard of care.

### **Criteria to discontinue Investigational Drug due to possible drug induced liver injury**

- ALT or AST >8xULN
- ALT or AST >3xULN and (TBL >2xULN or International Normalized Ratio (INR) >1.5)
- ALT or AST >3xULN with the appearance of fatigue, nausea, vomiting, right upper quadrant pain or tenderness, fever, rash, and/or eosinophilia (>5%)

If the patient reaches the above criteria to discontinue investigational medication the blind will not be broken, except in the case of patient safety concerns. All trial subjects showing possible investigational drug-induced liver injury will be followed until all abnormalities return to normal or to the baseline state, until declared clinically insignificant or until the status is declared as unresolved. However, no subjects will be followed-up beyond the final study follow-up visit.

### *6.7.3 Steroid Administration*

---

Intravenous methylprednisolone sodium succinate (MPSS) administration will be permitted in the study according to the discretion of the site specific principal investigator. However, when administered, only the dosing regimen prescribed by the second National Spinal Cord Injury Study will be permitted:

- MPSS IV 30mg/kg bolus given over first hour, followed by 5.4 mg/kg/hour for 23 hours

### *6.7.4 Blinding*

---

Subjects, Investigators, and study research personnel will be blinded to the subject treatment arm allocation. The AOSpine North America Methods Core will maintain link between the randomization information and the Investigational Drug information. This information will be accessible only to selected restricted personnel at the Methods Core, which will not include study monitors or other personnel in direct contact with the study sites. Treatment allocation will be un-blinded for the purpose of interim analysis presented to the DSMB. The results of the interim analysis and the un-blinded data will not be shared with Investigators, subjects or those involved in the execution of the study. Emergency un-blinding for the safety reasons will be permitted. Sites will be supplied with emergency un-blinding materials.

### *6.7.5 Enrollment*

---

Subject enrollment occurs at the time of Randomization. If a subject is consented, screened and for any reason does not get randomized, the subject will NOT be considered enrolled in the study.

The randomization will occur by opening the lowest sequential number of the sealed randomization envelopes at each specific site. Inside the envelope there will be a unique subject randomization number. The authorized research staff will match the unique subject

randomization number with the number on the Investigational Drug container. The randomization will be recorded in the Randomization Log.

### *6.7.6 Follow-up Evaluations*

---

Subjects will be evaluated according to the schedule set forth in this clinical Protocol. The schedule includes enrollment; surgery;  $72 \pm 12$  hours post-injury; 7 days  $\pm$  1 day after enrollment; 14 days  $\pm$  2 days; discharge from acute care; 84 days  $\pm$  14 days; 180 days  $\pm$  30 days; and 365 days  $\pm$  45 days. The study will continue until the last enrolled subject reaches the 180-day follow-up. As a consequence, a portion of subjects will not have 365-day follow-up visit.

All follow-up schedules are based on “Day 0” which for this study is the day of screening/enrollment visit, except for the visit 72 hours post-injury.

### *6.7.7 Study Schematic*

---

The schedule of visits and data to be collected at each visit is shown in Table 1. All visits are preferred to be performed in the clinic. However, if the subject is unable to visit the clinic, a study investigator or an assigned examiner may visit the subject to collect the data. Data collection by phone and/or mail is not permitted.

**Table 1 Schedule of study activities**

|                                                        | Screening / Enrollment | Surgery (if applicable) | 72 hours ± 12 hours post-injury | 7 days ± 1 day post-enrollment | 14 days + 2 days | Discharge from Acute Care | 84 days ± 14 days | 180 days ± 30 days | 365 days ± 45 days | Unscheduled Visit |
|--------------------------------------------------------|------------------------|-------------------------|---------------------------------|--------------------------------|------------------|---------------------------|-------------------|--------------------|--------------------|-------------------|
| Sign ICD                                               | X                      |                         |                                 |                                |                  |                           |                   |                    |                    |                   |
| Health Information Release Form (if applicable)        | X                      |                         |                                 |                                |                  |                           |                   |                    |                    |                   |
| Review Inclusion/Exclusion                             | X                      |                         |                                 |                                |                  |                           |                   |                    |                    |                   |
| Obtain Demographics                                    | X                      |                         |                                 |                                |                  |                           |                   |                    |                    |                   |
| Screening Labs                                         | X                      |                         |                                 |                                |                  |                           |                   |                    |                    |                   |
| Clinical Labs                                          |                        |                         | X                               | X                              | X                |                           |                   |                    |                    |                   |
| Pregnancy Test (if applicable)                         | X                      |                         |                                 |                                |                  |                           |                   |                    |                    |                   |
| ISNCSCI                                                | X                      |                         | X                               |                                | X                |                           | X                 | X                  | X                  |                   |
| Randomization                                          | X                      |                         |                                 |                                |                  |                           |                   |                    |                    |                   |
| Dispense Investigational Drug                          | X                      |                         |                                 |                                |                  |                           |                   |                    |                    |                   |
| Complete Investigational Drug Log                      | X                      |                         |                                 |                                | X                |                           |                   |                    |                    |                   |
| Medication Compliance SW &              |                        |                         |                                 |                                | X                |                           |                   |                    |                    |                   |
| Charlson Comorbidity Score                             | X                      |                         |                                 |                                |                  |                           |                   |                    |                    |                   |
| Injury Severity Score                                  | X                      |                         |                                 |                                |                  |                           |                   |                    |                    |                   |
| SF-36v2.0™                                             | X §         |                         |                                 |                                |                  |                           | X                 | X                  | X                  |                   |
| EQ-5D                                                  | X §         |                         |                                 |                                |                  |                           | X                 | X                  | X                  |                   |
| Obtain & complete socio-economic & health behavior SWs | X                      |                         |                                 |                                |                  |                           |                   |                    |                    |                   |
| Obtain & complete medical history SWs                  | X                      |                         |                                 |                                |                  |                           |                   |                    |                    |                   |
| Spine Trauma Injury Data SW                            | X                      |                         |                                 |                                |                  |                           |                   |                    |                    |                   |
| Concomitant Medications                                | X                      | X                       | X                               | X                              | X                | X                         | X                 | X                  | X                  | X                 |
| Vital Signs                                            | X                      | X                       | X                               |                                | X                | X                         |                   |                    |                    |                   |
| Record Operative Data                                  |                        | X                       |                                 |                                |                  |                           |                   |                    |                    |                   |
| MRI**                                                  |                        |                         | X**                             |                                |                  |                           |                   |                    |                    |                   |
| SCIM                                                   |                        |                         |                                 |                                | X                |                           | X                 | X                  | X                  |                   |
| GRASSP                                                 |                        |                         |                                 |                                | X***             | X***                      |                   | X                  |                    |                   |
| Pain NRS                                               |                        |                         |                                 |                                | X                |                           | X                 | X                  | X                  |                   |
| Report AEs & SAEs (including intra-operative)          |                        | X                       | X                               | X                              | X                | X                         | X                 | X                  | X                  | X                 |
| Discharge Information                                  |                        |                         |                                 |                                |                  | X                         |                   |                    |                    |                   |
| Physical & Occupational Therapy                        |                        |                         |                                 |                                |                  | X                         | X                 | X                  | X                  |                   |
| Verify Data & Enter into eCRF within 48 hours*         | X                      | X                       | X                               | X                              | X                | X                         | X                 | X                  | X                  | X                 |

\*Data should be entered into the eCRF within 48 hours, but no later than 14 calendar days from collection; \*\*MRI between 48-72 hours at the discretion of the Investigator; & Medication compliance should be completed daily; \*\*\*GRASSP will be performed at 14 days or Discharge (whichever occurs first); § Recall of status prior to the injuryStudy Timeline

